### Study Limitations

This study presents several limitations that should be considered when interpreting the findings. First, participants will be recruited from a single residential care home and a day care center, which may limit the diversity and representativeness of the caregiver population. This recruitment strategy may introduce selection bias, as participants are likely to be linked to formal care services and may not reflect the experiences of caregivers who are not connected to such resources. Although recruitment from multiple centers was considered, it was not feasible due to logistical and resource constraints. Consequently, the generalizability of the findings may be limited, and results should be interpreted with caution when extrapolating to other caregiving contexts or populations.

Second, the subdivision of participants into groups according to caregiving context and family role may result in relatively small subgroup sizes. Although inferential statistical analyses will be conducted, comparisons involving subgroups will be interpreted cautiously and considered exploratory.

Finally, as this is a cross-sectional observational study, causal relationships between variables cannot be established. However, the use of a convergent mixed-methods design is expected to provide a more comprehensive understanding of caregivers’ experiences by integrating quantitative and qualitative data.

## 4. Ethics and Dissemination

### 4.1. Research Ethics Approval

This project was approved by the Research Ethics Committee of the Universidad Rey Juan Carlos (code: 041220246522024), prior to the start of the project. The ethical principles for medical research involving human subjects of the Declaration of Helsinki adopted at the 18th Assembly of the World Medical Association (WMA) (Helsinki, Finland, June 1964) and with the latest version revised at the 64th General Assembly of the WMA held in Fortaleza (Brazil) in October 2013 were followed. In addition, they comply with the legislation in force in our country, including Law 14/2007 on Biomedical Research and Royal Decree 223/2004.

### 4.2. Dissemination Policy

The results of this study will be disseminated through publication in high-impact, peer-reviewed journals and presentations at leading national and international scientific conferences to maximize visibility and impact within the research community.

### 4.3. Consent or Assent

In this study, written informed consent will be obtained from each resident or their legal guardians/family members. Moreover, participants will have the option to withdraw or revoke their informed consent at any stage of the study.

### 4.4. Risks and Benefits

Participation in this study is considered to involve minimal risk. However, given that the study explores caregiving experiences and includes a subgroup of participants who have experienced the loss of a relative with AD, there is a potential risk of emotional distress during the interviews, particularly when discussing sensitive topics such as caregiving burden, anticipatory grief, and bereavement.

To minimize this risk, interviews will be conducted by trained researchers with experience in qualitative research and communication skills. Participants will be informed in advance about the nature of the topics to be discussed and will be reminded that they may decline to answer any question or withdraw from the study at any time without any consequences. During the interviews, researchers will monitor participants’ emotional responses and will pause or stop the interview if signs of significant distress are observed.

Regarding participants who have experienced bereavement, only individuals who express willingness to discuss their experience and who do not present evident signs of severe emotional vulnerability at the time of recruitment will be included.

The potential benefits of the study include contributing to a better understanding of caregivers’ experiences, which may help to improve support strategies and healthcare interventions for caregivers of people with AD. Although participants may not receive direct personal benefits, some individuals may find participation meaningful, as it provides an opportunity to reflect on and share their experiences.

### 4.5. Trial Registration

-Name of registry: Understanding the Lived Experience and Bereavement of Caregivers of People With Alzheimer’s Disease (ALCARE)-ClinicalTrials.gov registration identifying number: NCT07251738.-Date of registration: November 2025.-Type of registration: anticipated.-Protocol version: v2.

## Figures and Tables

**Figure 1 healthcare-14-00899-f001:**
[figure not shown]
Convergent parallel mixed-methods design.

**Figure 2 healthcare-14-00899-f002:**
[figure not shown]
Participant Timeline.

**Table 1 healthcare-14-00899-t001:** Semi-structured question guide, Group 1.

Area Under Study	Questions	Justification
Diagnosis of AD	What was the process like leading up to your family member’s AD diagnosis?	To explore participants’ initial experiences and emotional responses at the time of diagnosis, as well as the beginning of the caregiving trajectory.
	How did you feel when your family member received the diagnosis?	
Caring for someone with AD before they moved to a residential care home	What was your daily routine like when caring for your family member?	To explore caregiving routines, emotional experiences, occupational balance, and perceived quality of life, as well as decision-making processes and anticipatory grief associated with role transitions.
	What barriers and facilitators did you encounter on a daily basis?	
	Do you think that caring for your family member on a daily basis had an impact on your life?	
	How would you describe your state of mind while caring for your family member?	
	How would you describe your quality of life while caring for your family member?	
	Do you feel that you have stopped doing activities that you used to do? Which ones?	
	How did you come to the decision to place your relative in a nursing home to continue their care?	
Caring for someone with AD who lives in a residential care home	How does your family member living in a nursing home impact your day?	To examine changes in daily life, roles, and occupational balance after institutionalization, as well as adaptation to new caregiving contexts.
	Has your daily life changed since your family member was admitted to the nursing home?	
	What barriers and facilitators do you encounter now that your family member is living in a residential care home?	
Closing Question	What else would you like to share that we have not yet discussed?	To allow participants to introduce additional relevant experiences or perspectives not covered in the interview.

**Table 2 healthcare-14-00899-t002:** Semi-structured question guide, Group 2.

Area Under Study	Questions	Justification
Diagnosis of AD	What was the process like leading up to your family member’s AD diagnosis?	To explore initial experiences and emotional responses at the onset of the disease.
	How did you feel when your family member received the diagnosis?	
Caring for someone with AD at home	What was your daily routine like when caring for your family member?	To examine caregiving experiences at home, including routines, emotional impact, occupational balance, and quality of life, as well as decision-making processes and anticipatory grief related to changes in care context.
	What barriers and facilitators did you encounter on a daily basis?	
	Do you think that caring for your family member on a daily basis had an impact on your life?	
	How would you describe your state of mind while caring for your family member?	
	How would you describe your quality of life while caring for your family member?	
	Do you feel that you have stopped doing activities that you used to do? Which ones?	
	How did you come to the decision to take your relative to a day center in a nursing home to continue their care?	
Closing Question	What else would you like to share that we have not yet discussed?	To allow participants to introduce additional relevant experiences or perspectives.

**Table 3 healthcare-14-00899-t003:** Semi-structured question guide, Group 3.

Area Under Study	Questions	Justification
Diagnosis of AD	What was the process like leading up to your family member’s AD diagnosis?	To explore early experiences and emotional responses at the beginning of the caregiving process.
	How did you feel when your family member received the diagnosis?	
Caring for someone with AD	What was your daily routine like when caring for your family member?	To explore caregiving experiences, including routines, emotional burden, occupational balance, and perceived quality of life, as well as anticipatory grief and role transitions during the caregiving period.
	What barriers and facilitators did you encounter on a daily basis?	
	Do you think that caring for your family member on a daily basis had an impact on your life?	
	How would you describe your state of mind while caring for your family member?	
	How would you describe your quality of life while caring for your family member?	
	Do you feel that you had stopped doing activities that you used to do? Which ones?	
	How did you come to the decision to place your relative in a nursing home to continue their care?	
Grief/Mourning	How have you been since the death of your family member?	To explore bereavement experiences, including emotional impact, meaning-making, changes in identity and daily life, and adaptation following loss.
	What has the loss of your family member meant to you?	
	To what extent do you think your life has changed since your loss? And in what ways?	
	Do you think your quality of life has changed now compared to when you were caring for your relative?	
	What lessons did you learn from caring for your family member?	
	How do you envision your life moving forward?	
Closing Question	What else would you like to share that we have not yet discussed?	To allow participants to introduce additional reflections, including aspects of grief, meaning, or unmet needs.

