## 2. Materials and Methods

### 2.1. Study Design

For this project, a mixed-methods parallel convergent study will be designed. The purpose of mixed-methods research is to provide comprehensive and contextualized answers to questions raised in the health sciences, integrating different approaches to compensate for the limitations inherent in a single method or methodological perspective, through the parallel or simultaneous collection and analysis of qualitative and quantitative data [15].

A convergent design is particularly suitable for this study because the impact of caring for a person with AD involves both measurable outcomes and complex subjective experiences. Quantitative methods allow the assessment of caregiving burden, occupational balance, role performance, and quality of life, while qualitative approaches enable the exploration of caregivers’ lived experiences, perceptions of caregiving, and grief processes. The use of a convergent design will allow both types of data to be collected during the same phase of the study, analysed independently, and subsequently integrated to provide a more comprehensive understanding of caregivers’ experiences [15].

To this end, a quantitative observational cross-sectional study (QUAN) and a qualitative case study (QUAL) will be designed, with data collection and analysis for both methods carried out simultaneously. Qualitative case studies offer the opportunity to investigate in depth different perspectives of a specific health and disease phenomenon in its real context, using the perspective of people in their own social environment [19]. Cross-sectional studies, being observational in nature, offer a snapshot of the characteristics of subjects at a given point in time. However, they lack a follow-up period, which prevents the establishment of cause-and-effect relationships [20].

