#### 2.2.2. Inclusion Criteria

To carry out this study, three groups of relatives of people diagnosed with AD will be formed.

*Inclusion criteria for Group 1:* relatives of people diagnosed with AD by a neurologist or geriatrician; who have their relative institutionalized in a nursing home; who agree to participate voluntarily in the project; and who have signed the informed consent form.

*Inclusion criteria for Group 2:* relatives of people diagnosed with AD by a neurologist or geriatrician; who live with and/or care for the person with AD; who attend a Day Center or a rehabilitation center; who agree to participate voluntarily in the project; and who have signed the informed consent form.

*Inclusion criteria for Group 3:* relatives of people diagnosed with AD by a neurologist or geriatrician; who have suffered the loss of a relative with AD; who have lived with and/or cared for the person with AD until the end of their life; who agree to participate voluntarily in the project; and who have signed the informed consent form.

In addition, after accepting participation in the QUAN design, participants will be offered the opportunity to participate in the QUAL design. For the subdivision of the groups, participating family members will be divided based on kinship:Subgroup 1: husband or wife.Subgroup 2: daughter or son.Subgroup 3: grandson or granddaughter.

These case groups have been selected based on the different roles assumed by various family members, with the aim of exploring experiences in different family contexts and existing generational differences.

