### 2.7. Procedure for Integrating Quantitative and Qualitative Data

Data integration will be carried out using a mixed concurrent design, in which QUAN and QUAL data collection and analysis will be performed simultaneously [36]. The integration process will consist of interpreting and presenting the findings through joint narratives and joint displays [51,52,53].

Once the independent analysis of each component has been completed, the researchers will jointly integrate the results. The findings from the QUAN and QUAL phases will be presented together in the same section, supported by a table illustrating the integration of the data.

Integration will follow a side-by-side comparison approach, in which quantitative results (e.g., caregiving burden, occupational balance, and quality of life scores) will be aligned with qualitative themes derived from participants’ narratives (e.g., perceived role changes, daily life impact, and experiences of grief). This approach is commonly used in convergent mixed-methods designs to directly compare and relate findings from both datasets [54,55]. This process will allow the identification of areas of convergence (agreement between quantitative and qualitative findings), complementarity (where qualitative data help to explain or expand quantitative results), and divergence (inconsistencies between datasets), as described in mixed-methods integration frameworks [51,52,53].

The integration of both datasets will support the development of meta-inferences, contributing to a more comprehensive understanding of caregivers’ occupational lives and well-being [54,55].

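### In Group 1, quality of life and state of mind are asked about only for the time before nursing-home admission, but the SF-36 and ZBI set beside those answers are completed after it

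*Protocol article*

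**What the plan says.** Section 2.2.2 of the protocol article defines Group 1 as relatives "who have their relative institutionalized in a nursing home". Section 2.1 describes the quantitative strand as cross-sectional; such studies "offer a snapshot of the characteristics of subjects at a given point in time". No measurement before admission is planned.

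Table 1 gives the Group 1 interview guide question by question. Under "Caring for someone with AD before they moved to a residential care home" it lists, among others, "How would you describe your state of mind while caring for your family member" and "How would you describe your quality of life while caring for your family member". The block on life with the relative in residential care has three questions: effect on the caregiver's day, change in daily life since admission, and current barriers and facilitators.

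Table 1's justification column assigns emotional experience and perceived quality of life to the earlier block. To the later block it assigns daily life, roles, occupational balance and adaptation.

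Section 2.7 states that "quantitative results (e.g., caregiving burden, occupational balance, and quality of life scores) will be aligned with qualitative themes", and that the comparison will identify convergence, complementarity and divergence. The Discussion adds emotional experiences to the themes to be examined beside the scores. Neither place says that score and theme should refer to the same period.

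**The concern.** A side-by-side comparison is informative when both sides describe the same state of the same people. For quality of life and emotional burden in Group 1, the guide prompts an account of home care that has ended, while the questionnaires are filled in during residential care. Between the two lies the placement, which is the contrast the study wants to understand under Objectives 4 and 7.

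If caregivers' circumstances changed with placement, good current scores beside a difficult narrative could be read as the two methods disagreeing when both are accurate for their own period. Apparent agreement is exposed in the same way: poor scores now and a hard account of then may match for unrelated reasons. An account of the present that was not elicited at interview would also be hard to recover later.

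**Working it through.** No sample-size, power or error-rate figure bears on this point. The check compares the period that each source addresses.

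**1. Period of the scores.** Group 1 eligibility requires that the relative is already in the nursing home (section 2.2.2), and there is one assessment (section 2.1). The ZBI, SF-36, OBQ and Role Checklist are therefore completed after admission. The article gives no recall periods for the ZBI, SF-36 or OBQ. That the SF-36 and ZBI describe the current state is inferred from the design.

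**2. Period of the interview questions.** Table 1 has 2 (diagnosis) + 7 (before admission) + 3 (after admission) + 1 (closing) = 13 questions. By construct:

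| Construct | Before-admission block | After-admission block |
|---|---|---|
| Quality of life | 1 | 0 |
| State of mind | 1 | 0 |
| Activities given up | 1, but worded up to the present | 0 |
| Daily routine, impact or change | 2 | 2 |
| Barriers and facilitators | 1 | 1 |

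The seventh question in the before-admission block concerns the decision to place the relative.

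The activities question reads "Do you feel that you have stopped doing activities that you used to do? Which ones". Table 3 puts the same question to bereaved relatives in the past perfect. The Group 1 wording can thus draw an answer about the present despite its position. That leaves two constructs with a before-admission question only: quality of life and state of mind.

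**3. Which scores are affected.** Quality of life pairs with the SF-36. State of mind pairs with the emotional side of the ZBI. The OBQ and Role Checklist have same-period material, because the later block is meant to cover roles and occupational balance after admission.

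**4. Whether another passage closes the gap.** Section 2.7 and the Discussion set out the alignment with no reference to period. Table 3 asks bereaved relatives whether their quality of life differs now from when they were caring. Group 1 has also been through a transition and gets no such question.

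**5. Share of the integration.** Section 2.2.1 plans 12 interviews in each of three groups. Section 2.1 places only the home-care and nursing-home groups in the quantitative strand. Interviews in groups with both data types: 12 + 12 = 24. Group 1's share: 12/24 = one half.

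**The case against.** The strongest reply is that the guide is not a fixed questionnaire. Section 2.4 says it will be used flexibly, with order and depth adapted to the participant, and describes it as covering care before and/or after institutionalization. A pilot interview will test the relevance of the questions, and an open closing question invites anything missed. A caregiver asked how daily life has changed since admission may well speak about mood and quality of life. The integration is also interpretive: section 2.7 lets qualitative material explain or expand a score, so an account of hard home care followed by relief could properly be classed as complementarity.

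All of this stands as mitigation. It makes a current account possible but does not secure one. Section 2.4 also says that not every question need be asked, and flexibility does not tell the analyst which period a passage describes.

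The reply is right against several stronger readings that a reader might infer:

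- **The whole Group 1 integration mixes periods.** It does not. Table 1 has a dedicated after-admission block, and two of the theme examples in section 2.7, role changes and daily-life impact, are covered there.
- **The plan predicts improvement after placement and will therefore produce divergence.** The hypothesis in section 1.1.3 compares two groups of caregivers, not the same caregivers before and after, and section 2.7 does not assign divergence mechanically.
- **Objective 7 cannot be answered.** Group 1 caregivers are asked about the placement decision and life afterwards, which is direct evidence on caregiving context. The objective is weakened for two constructs, not lost.
- **The past tense in Table 2 is the same fault.** Group 2 has no admission to separate two periods, so that is a matter of wording.

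**Conclusion.** The point holds in a limited form. In Group 1, quality of life and state of mind have one question each before admission and none after, while the SF-36 and ZBI are completed after admission and will be aligned with the themes without regard to period. For these two constructs, agreement or divergence in the joint display could come from the difference in period.

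The direction and size of any distortion cannot be derived from the document. The conclusion assumes that the SF-36 and ZBI are answered about the caregiver's current state and that interviewers broadly follow the printed blocks. The period of the two questions is set by their block heading rather than by their own wording. This is an inexpensive improvement to make before interviewing starts, not a failure of the design.

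**What to change.** In Table 1, add two questions in the present tense to the residential-care block, one on quality of life and one on state of mind. Alternatively, use a now-versus-then question like the quality-of-life one in Table 3, extended to state of mind. Amend that block's justification to match.

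In section 2.7, state that Group 1 interview material will be labelled as before or after admission in the joint display, and that SF-36 and ZBI results will be compared with the after-admission accounts. Before-admission material stays in the display as context. The Role Checklist should not be tied to one period, because section 2.4 describes it as covering past, current and future roles.

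The cost is a few more minutes in each of 12 interviews, probably within the planned 45–80 minutes, plus one extra code in MAXQDA and notification of the revised guide to the ethics committee.

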## Data Availability

No new data were created or analyzed in this study. Data sharing is not applicable to this article.

## Abbreviations

The following abbreviations are used in this manuscript:

AD	Alzheimer’s disease
WHO	World Health Organization
ADL	Activities of Daily Living
QUAN	Quantitative study
QUAL	Qualitative study
ZBI	Zarit Burden Interview
OBQ	Occupational Balance Questionnaire
SF-36 QoL-Q	Short Form-36 Health Survey Quality of Life Questionnaire
DMC	Data Monitoring Committee
WMA	World Medical Association
